**- Randomization:**

After providing written informed consent, a random allocation sequence will be carried out using the Epidat program. The participants will be randomly allocated into intervention group, control group without music, or control group with music.

The groups are the followed:

- Intervention group or TG (participants that use specific composed music as an adjunct to chest physiotherapy routine).
- Control group without music or CG (participants that do not use music as an adjunct to chest physiotherapy routine).
- Control group with music or PG (participants that use commercial music as an adjunct to chest physiotherapy routine).

Participants in every group will continue with their usual treatment regimen without modifications.

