### Secondary objectives:

- To evaluate the effects of music therapy as an adjunct to chest physiotherapy on enjoyment, perception, adherence to daily chest physiotherapy of patients and family members.
- To evaluate the effects of music therapy as an adjunct to chest physiotherapy on pulmonary symptomatology and quality of life.

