**- Inclusion criteria:**

- Diagnosis of cystic fibrosis based on international criteria (Aldana et al, 2011).
- Children between ages of 2-17.
- Undergoing periodic clinic visits in the cystic fibrosis Unit.
- Understanding the purpose of the study.
- To provide written informed consent.

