**- Data collection:**

Demographic and clinical data will be collected in the case report formulary from each participant (Annex). Specifically: age, gender and respiratory infection exacerbations that requiring hospitalization.

These participants are controlled in the Pediatric Pulmonology Unit at Malaga Regional Hospital, where each child with cystic fibrosis has a detailed clinic history, being the clinical variables systematically included and the treatment updated. Therefore, the present study does not imply additional clinic information collection. Demographic and clinical information will be completed by Pediatricians during the usual follow-up.

In addition, participants will complete a baseline and 2 evaluation questionnaires during the trial-period in order to know children's and family members' chest physiotherapy perception. The questionnaires will be conducted about chest physiotherapy experiences to evaluate the evolution of their perceptions during the trial-period. These questionnaires are designed specifically to know evolution of CPT characteristics such as, enjoyment and perception or time or adherence to daily chest physiotherapy, after the use of music therapy as an adjunct to CPT (Grasso et al, 2000). The perception of pulmonary symptomatology and the impact on the quality of life will be also evaluate using a visual analog scale (VAS) to assess the magnitude of dyspnea in pulmonary diseases such as CF (Bausewein et al, 2007) and the revised cystic fibrosis quality of life questionnaire (Quittner et al, 2000), respectively.

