#### **- Intervention:**

After participant recruitment they will complete the baseline questionnaire and be asked to carry out the CPT routine during 6 weeks (Grasso et al, 2000; Canga et al, 2015) as follow:

- Intervention group or TG: Using the Music-CD as an adjunct to each part of the CPT routine. The Music-CD will be provided after baseline questionnaire.
- Control group without music or CG: Continuing with the usual CPT without modifications.
- Control group with music or PG: Using commercial music as an adjunct to each part of the CPT routine.

As has been comment, the CPT treatment in this Unit is divided into 3 sections with a total length of about 40 minutes: During the first part, children should be relaxed while the nebulizer inhalation treatment is applied around 10-15 minutes. Next, airway clearance techniques are administered during 20-30 minutes to promote mucus expulsion. Finally, a new relaxation phase of about 5 minutes is proposed, where antibiotic nebulizer treatment is administered if necessary.

Participants in every group will continue with their usual treatment regimen without modifications. Follow-up changes or treatments modifications are not planned in any case.

A second questionnaire will be completed after 6 weeks and participants will continue managing the CPT routine in the same way during a new 6-week period. After that, the final questionnaire will be completed (Grasso et al, 2000) and the music-CD will be offered to CG and PG participants.

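### The plan does not ensure that baseline ratings come before the family knows its arm, and the questionnaire does not record whether the child or a family member answered

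*Combined protocol and SAP*

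**What the plan says.** All places are in the combined protocol and SAP.

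- **Allocation.** The Randomization section ties it to consent: "After providing written informed consent, a random allocation sequence will be carried out using the Epidat program". It continues: "The participants will be randomly allocated into intervention group, control group without music, or control group with music". No concealment, stratification or blocking is described.
- **Baseline.** The Intervention section says: "After participant recruitment they will complete the baseline questionnaire". For the intervention group it adds: "The Music-CD will be provided after baseline questionnaire". It gives no matching timing for the commercial music used by the music control group.
- **Who is studied.** Inclusion criteria: "Children between ages of 2-17". The first secondary objective covers enjoyment, perception and "adherence to daily chest physiotherapy of patients and family members". Data collection also wants the perceptions of both children and relatives, and says "participants will complete a baseline and 2 evaluation questionnaires during the trial-period".
- **The form.** The Annex questionnaire has one set of items. It has no place to enter who answered, no child and family versions, no age for self-report, and no rule on keeping the same respondent.
- **The analysis.** The Statistical analysis section compares evolution across arms in a repeated-measures model with group and time as its only factors, and tests baseline against final values within each group by the Wilcoxon test. Age is collected but does not enter the model. Child and family answers are not distinguished.

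**The concern.** The sample size rests on perceived session time, which the respondent estimates without blinding to the arm. Enjoyment, dyspnoea and symptom frequency are also the respondent's own ratings. Every change is measured from the baseline form. If a family knows its arm when it fills in that form, hope or disappointment can move the baseline, and the arms then differ in change without any effect of the music. Holding back the CD prevents exposure to it, but not knowledge of the arm.

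The second gap concerns what is measured. A 2-year-old cannot estimate minutes or use a scale from -3 to +3, so an adult must answer for some children, while a 17-year-old can answer alone. Without a respondent entry, the objective for patients and family members cannot be examined separately. If a parent fills in one form and the child the next, the difference between the two people is recorded as change over time. Neither problem can be repaired after the data are collected.

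**Working it through.** **Inputs.** From the Sample size section: SD 10.2 minutes, target difference 8 minutes, 13 per group, 80% power, 95% confidence. From the inclusion criteria: ages 2 to 17. Everything marked *assumed* is not in the documents.

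**The plan's own figure.** (10.2 × (1.960 + 0.842) / 8)² = 12.76, rounded up to 13; 3 × 13 = 39. This one-sample (or paired) two-sided normal formula reproduces the stated size. It is used below only as the arm size; this point does not change it.

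**1. Order of steps.** Randomization gives consent, then allocation. Intervention gives recruitment, then baseline form, then CD. Set side by side, they leave two sequences open: consent, allocation, baseline, CD; or consent, baseline, allocation, CD. Both comply with the text, and only the second protects the baseline.

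**2. What a shifted baseline would do.** *Assumed:* change-score SD 10.2, no true effect, and knowledge of the arm moves one arm's mean baseline by b minutes. The standard error of an arm difference is 10.2 × √(2/13) = 4.00, so the noncentrality is b / 4.00, on 24 degrees of freedom.

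| b (minutes) | b / 4.00 | Rejection rate at 5%, two-sided |
|---|---|---|
| 1 | 0.25 | 5.7% |
| 2 | 0.50 | 7.7% |
| 4 | 1.00 | 16% |

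**3. What a change of respondent would do.** *Assumed:* child and parent differ by D minutes, and a net k of 13 in one arm switch in the same direction between forms. The arm's mean change moves by kD/13. With k = 4:

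- D = 2: 8/13 = 0.6 minutes
- D = 5: 20/13 = 1.5 minutes
- D = 8: 32/13 = 2.5 minutes

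The target is 8 minutes. If switching is balanced across arms, the arm contrast is spared, but the within-group Wilcoxon tests are not.

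**4. Age.** *Assumed:* ages spread evenly over 2 to 18 (exact age) and three arms of 13. The age SD is 16/√12 = 4.62, and the standard error of a difference in mean age is 4.62 × √(2/13) = 1.81 years. For one given pair of arms, a gap above 2 years (z = 2/1.81 = 1.10) has probability about 27%, and above 3 years (z = 1.66) about 10%. For the worst of the three pairs, simulation gives 51% and 22%. Counts under 8 years, a cut-off that is not in the documents, differ by 4 or more between some pair in 32 to 33% of allocations. These figures describe chance imbalance only.

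**5. Does age imbalance carry into the planned comparison?** With an assumed stable parent-child level difference of 5 or 8 minutes, a constant respondent and no treatment effect, simulated change-score ANOVAs rejected in 5.1% and 4.8% of trials, which is the nominal rate. A stable level difference cancels in within-subject change. Age matters to the comparison only if the change itself depends on age, or if the respondent switches.

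**The case against.** The strongest reply is that these are silences and not faults. Consent must come before any trial questionnaire, so allocation after consent is compatible with a baseline taken first. The Intervention section reads naturally as recruitment, baseline, instruction, CD. A reader might infer that the plan sets disclosure before baseline. It does not; it leaves the order open. What stands is that nothing in the text prevents the harmful order, and that the CD safeguard covers one arm and exposure only.

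A reader might also infer that child and parent answers are to be pooled. No section says so. What stands is that the form gives no means of keeping them apart.

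On age, a reader might take the 51%, 22% and 32% figures as evidence of bias, or as a reason why stratified blocks are required. Unstratified randomization is valid in expectation, the figures are for the worst of three pairs under an assumed age spread, and step 5 shows that stable differences cancel. With 39 children, stratification is a preference.

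Nor are all outcomes other than hospitalisation ratings of feeling: routine frequency, sessions per day, length and interruptions are reported behaviours. They still depend on who reports them.

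Finally, choosing one respondent per child by age would confound respondent with age and leave the parents of older children unmeasured. That is right, and it is why the fix asks for two copies where both views are wanted.

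**Conclusion.** The point holds in a limited form. The respondent gap is firm: on the form as written, child and proxy answers are inseparable and a switch of respondent is undetectable, although the objectives name both patients and family members. The timing gap is an omission to be closed: the plan does not guarantee that baseline ratings precede knowledge of the arm.

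The size of either effect cannot be derived from the documents. Under the stated assumptions, a baseline shift of 1 to 4 minutes raises the rejection rate under no effect from 5% to between 5.7% and 16%, and a net switch of 4 of 13 respondents moves an arm's mean change by 0.6 to 2.5 minutes. Age imbalance is a chance matter, best handled in the model; it is not shown to bias the comparison.

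**What to change.** - **Randomization and Intervention:** state that the allocation is disclosed to the family only after the baseline questionnaire has been handed in. This also settles the start of commercial music in the music control group.
- **Annex questionnaire:** add a respondent field (child, or parent/family member) and require the same respondent at all three time points. Where both perceptions are wanted, use one copy for the child and one for the family member.
- **Statistical analysis:** add age as a continuous covariate, with its interaction with time, to the repeated-measures model. The interaction is the part that can adjust the comparison of evolution. Report results by respondent type as descriptive only, since each type will be a fraction of 13 per arm.

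Cost: the order of two existing steps, one form field or an extra copy, and a degree of freedom or two. With 39 children in three groups, the between-subject error falls from 39 - 3 = 36 to 35, and the within-subject error over three time points from 2 × 36 = 72 to 2 × 35 = 70. No visits are added. Stratified blocks and an age cut-off are optional and not needed for this point.

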**- Data collection:**

Demographic and clinical data will be collected in the case report formulary from each participant (Annex). Specifically: age, gender and respiratory infection exacerbations that requiring hospitalization.

These participants are controlled in the Pediatric Pulmonology Unit at Malaga Regional Hospital, where each child with cystic fibrosis has a detailed clinic history, being the clinical variables systematically included and the treatment updated. Therefore, the present study does not imply additional clinic information collection. Demographic and clinical information will be completed by Pediatricians during the usual follow-up.

In addition, participants will complete a baseline and 2 evaluation questionnaires during the trial-period in order to know children's and family members' chest physiotherapy perception. The questionnaires will be conducted about chest physiotherapy experiences to evaluate the evolution of their perceptions during the trial-period. These questionnaires are designed specifically to know evolution of CPT characteristics such as, enjoyment and perception or time or adherence to daily chest physiotherapy, after the use of music therapy as an adjunct to CPT (Grasso et al, 2000). The perception of pulmonary symptomatology and the impact on the quality of life will be also evaluate using a visual analog scale (VAS) to assess the magnitude of dyspnea in pulmonary diseases such as CF (Bausewein et al, 2007) and the revised cystic fibrosis quality of life questionnaire (Quittner et al, 2000), respectively.

**- Study variables:**

- Demographics:
  - Age (quantitative variable) (unit: years)
  - Gender (qualitative, dichotomous variable) (male / female)
- Clinics:
  - Number of respiratory infection exacerbations that requiring hospitalization (quantitative variable)
  - Days of hospitalization per exacerbation (quantitative variable)
- Chest physiotherapy characteristics:
  - Use of activities to accompany the routine (qualitative, dichotomous variable) (yes /no)
  - Type of activities used to accompany the routine (toys, stories, music, radio, TV...) (qualitative variable)
- Chest physiotherapy adherence:
  - Routine frequency (quantitative variable)

- Number of times per day (quantitative variable)
- Interruptions (qualitative, dichotomous variable) (yes /no)
- Length per session (quantitative variable)
- Chest physiotherapy attitude:
  - Response to the routine using a Likert scale (-3 to +3): least enjoyment – neutral - most enjoyment (quantitative variable)
  - Feelings about the routine choosing 3 words to describe these feelings (qualitative variable)
- Perception of time taken to complete the chest physiotherapy:
  - Perception of being a long routine (qualitative, dichotomous variable) (yes /no)
  - Time that seems to need the routine (quantitative variable)
- About the music:
  - Music use frequency (quantitative variable)
  - Response to the use of music during routine using a Likert scale (-3 to +3): least enjoyment – neutral - most enjoyment (quantitative variable)
  - Usefulness of music during routine (qualitative, dichotomous variable) (yes /no)
  - How music has been useful (qualitative variable)
  - To continue using this music as an adjunct to the routine in the future (qualitative, dichotomous variable) (yes /no)
- Perception of pulmonary symptomatology and impact on quality of life:
  - Measurement of the symptoms of dyspnea using a dyspnea visual analog scale (VAS), being 1 no dyspnea and 7 maximal dyspnea.
  - Frequency of respiratory symptoms according to the revised quality of life questionnaire for cystic fibrosis during the previous 2 weeks: cough during the day and night, expectoration and type of expectoration, breathing difficulties, whistling sounds when breathing, and respiratory congestion.

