### **Collaborating researchers:**

[name] [name], PhD. Department of Pharmacology and Pediatrics, Faculty of Medicine, Malaga University. Biomedical Research Institute of Malaga (IBIMA), Malaga, Spain. Unit of Pediatric Pulmonology, Malaga Regional Hospital, Malaga, Spain.

[name] [name]. Physiotherapist specialist in children chest physiotherapy. Department of Pharmacology and Pediatrics, Faculty of Medicine, Malaga University, Biomedical Research Institute of Malaga (IBIMA), Malaga, Spain.

[name] [name]. Professional musician and music teacher of children. Department of Pharmacology and Pediatrics, Faculty of Medicine, Malaga University. Biomedical Research Institute of Malaga (IBIMA), Malaga, Spain. Department of Education. Andalusian Government, Malaga, Spain.

**Objective:** To develop a strategy based on music therapy as adjunct to daily chest physiotherapy in children with cystic fibrosis and to evaluate its effects.

**Study design:** Interventional - randomized controlled trial. Single center: Unit of Pediatric Pulmonology, Malaga Regional Hospital.

**Disease or disorder under study:** Cystic fibrosis.

**Participants:** Children between ages of 2-17 from the Pediatric Pulmonology Unit at Malaga Regional Hospital. The sample size determined in each group is 13 participants. A total of 39 participants are necessary.

**Total study period:** Two years.

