**- Sample size:**

To calculate the sample size, the perception of time taken to complete the routine has been assumed as main variable. According to Grasso et al, (2000) where the control group values in this variable were  $0.2 \pm 10.2$  (mean  $\pm$  SD), considering these values as baseline, a power of 80 %, a confidence level of 95 %, and a similar variability at the end of the study, a difference of 8 minutes would be considered as statistically significant with a sample size of 13 subjects. A total of 39 participants are necessary.

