#### **- Statistical analysis:**

Statistical analysis will be performed using SPSS Software.

Initially a descriptive analysis of the study variables will be carried out, the values of the continuous variables will be summarized in a table where their corresponding means and standard deviation will be shown. The categorical variables will be presented in absolute and relative frequencies.

To compare qualitative measures Chi-square or Fisher tests will be used, and ANOVA or Kruskal-Wallis tests to quantitative.

To contrast the differences in the evolution of the variables between the different groups the multivariate analysis of variance test of repeated measures (MANOVA) will be applied with a factor between subjects (group) and a factor intra subjects (different moments of the intervention). Depending on the compliance of the sphericity condition, the Greenhouse-Geisser correction will be used. To contrast the differences between baseline and final measures in each group Wilcoxon test will be applied. To compare response to using music after the intervention into TG and PG, Mann–Whitney U test was used.

To compare response to using music after the intervention into TG and PG, Mann–Whitney U test will be used.

A significance of 5% ( $p < 0.05$ ) will be required to consider a difference as statistically significant.

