#### ANNEX - CASE REPORT FORMULARY

Age:

Gender:

Respiratory infection exacerbations that requiring hospitalization:

|                                    | Pre-study period | Study-period |
|------------------------------------|------------------|--------------|
| Number of exacerbations            |                  |              |
| Days hospitalized per exacerbation |                  |              |

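### Length of stay per exacerbation has no defined value for a child who is not admitted; total hospital days per randomised child would be the sounder variable (low severity)

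*Combined protocol and SAP*

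**What the plan says.** The protocol's Study variables section has two clinical items: "Number of respiratory infection exacerbations that requiring hospitalization (quantitative variable") and, directly below it, "Days of hospitalization per exacerbation (quantitative variable"). The case report form in the Annex repeats the second as "Days hospitalized per exacerbation", with one cell for the time before the study and one for the study period.

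The Statistical analysis section assigns tests by type of variable. For comparisons between arms it gives "ANOVA or Kruskal-Wallis tests to quantitative". For change within an arm it says "To contrast the differences between baseline and final measures in each group Wilcoxon test will be applied".

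No section says what is entered for a child who was not admitted, how several stays in one child are combined, or which children enter the comparison. No variable for total hospital days per child is defined, and no admission rate is given.

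**The concern.** A length of stay per exacerbation is a ratio whose denominator is itself an outcome. When a child has no hospitalised exacerbation there is nothing to divide by. Taken at face value, such a child has a blank cell and drops out of the ANOVA or Kruskal-Wallis test.

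The children left are then defined by something that happens after randomisation. The Hypothesis and Ethical considerations sections reason from music to adherence, to airway clearance, to preserved lung function, so an effect on admissions is plausible even though it is not a stated aim. If one arm avoided some admissions, the admitted children in the three arms would no longer be comparable groups. Were the avoided admissions mainly the shorter ones, mean stay would rise in the arm that did better. The number of children involved could also be very small.

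**Working it through.** The documents give no figure for hospital days, so there is none to reproduce. The 13 per arm was derived for another variable ("the perception of time taken to complete the routine has been assumed as main variable") and is used here only as the arm size.

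**Inputs**
- Arm size, from the opening summary: "The sample size determined in each group is 13 participants. A total of 39 participants are necessary". This gives three arms of 13.
- Window, from the Intervention section: a first 6 weeks, after which "participants will continue managing the CPT routine in the same way during a new 6-week period". So 6 + 6 = 12 weeks. Reading the form's study-period column as these 12 weeks is an assumption.
- Admission rate r per child-year: not in the documents. Assumed 0.25, 0.5 and 1, with 2 as a stress case, constant over time, independent between children and equal in all arms.

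**Step 1. How many children would have a value**

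Chance of at least one admission: p = 1 − exp(−r × 12/52).
Expected children with a value: 13p per arm, 39p overall.
Chance that a given arm has fewer than two: q = (1−p)^13 + 13p(1−p)^12.
Chance that at least one of three arms has none: 1 − [1 − (1−p)^13]^3.
Chance that at least one of three arms has fewer than two: 1 − (1−q)^3.

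| r | p | 13p | 39p | Given arm < 2 | Some arm has 0 | Some arm < 2 |
|---|---|---|---|---|---|---|
| 0.25 | 0.056 | 0.73 | 2.19 | 0.84 | 0.85 | 0.996 |
| 0.5 | 0.109 | 1.42 | 4.25 | 0.58 | 0.53 | 0.925 |
| 1 | 0.206 | 2.68 | 8.04 | 0.22 | 0.14 | 0.52 |
| 2 | 0.370 | 4.81 | 14.42 | 0.02 | 0.007 | 0.06 |

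Under this model p reaches one half at r = ln 2 × 52/12 = 3.0 per child-year. Below that rate, most children would have no value.

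**Step 2. Can the direction change?** (hypothetical figures)

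Take an arm of 13 in which three children are admitted once each, for 5, 5 and 14 days. In a second arm, otherwise the same, both 5-day admissions are prevented.

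| Summary | First arm | Second arm |
|---|---|---|
| Days per exacerbation, admitted only | 24/3 = 8.0 | 14/1 = 14.0 |
| Days per child, 0 if not admitted | 24/13 = 1.85 | 14/13 = 1.08 |
| Number of admissions | 3 | 1 |

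By the first row the better arm looks 75% worse (14.0/8.0 = 1.75). By the second and third rows it looks better. Each child here has at most one admission, so the first two rows differ only in whether a blank or a 0 is entered. The unwritten rule settles the direction in this example.

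**Step 3. Several admissions**

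For a child with stays of 5 and 14 days, the single cell could hold the mean (19/2 = 9.5), the total (19) or both stays. The form does not say which.

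**Step 4. Within-arm test**

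If the Wilcoxon test is applied to this variable, a child needs an admission in both periods to contribute a pair. That is a smaller group than in Step 1. The length of the pre-study period is not stated.

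**The case against.** The case against giving this much weight is strong in several respects.

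- **Exclusion is not written down.** A reader might infer that the plan drops children who were not admitted. It does not say so; it is silent, and staff might enter 0. This stands: what the documents show is a missing rule. But a 0 would no longer be a stay per exacerbation, and Step 2 shows that the choice can matter.
- **No rate is given and the window is not defined on the form.** A reader might infer that most children will certainly have no value. The documents do not establish that. The form does not define its study period, and the opening summary gives two years as the total study period. The counts in Step 1 hold only under the stated assumptions.
- **Admissions are not a stated target.** The hypothesis and objectives name enjoyment, perception, adherence, pulmonary symptoms and quality of life. The Data collection section groups hospitalised exacerbations with age and gender as routine data. This stands and limits the weight of the point.
- **The count is already there.** It is defined for every child, and in Step 2 it would show the fall from 3 to 1 at once. This stands. Total days can also be recovered if each stay, or the mean, is recorded, although the form does not secure that.
- **The reversal is constructed.** It needs the shorter stays to be the ones prevented, and three admissions in an arm match only the top of the 0.25 to 1 range (13 × 1 × 12/52 = 3.0). A reader might infer that the intervention arm will look worse. Nothing in the documents makes that likely; it is only possible.

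**Conclusion.** The point holds as a low-severity one. The variable is listed for testing without a value for children who have no admission and without a rule for several. Its literal reading compares a subset formed after randomisation. With 13 children per arm, a 12-week window and assumed rates of 0.25 to 1 admission per child-year, about 0.7 to 2.7 children per arm would contribute. The chance that a given arm has fewer than two runs from 84% down to 22%. Even at 2 per child-year, fewer than 5 of 13 are expected. Such a comparison could mislead, and could do so in direction.

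The reach is limited. The variable did not set the sample size and is not named in the hypothesis, so no headline conclusion depends on it. The documents do not support saying that the plan excludes children who were not admitted, or that a reversal is to be expected.

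**What to change.** Replace the variable with total days hospitalised for respiratory exacerbation during the 12-week study period, per randomised child, with 0 for a child who was not admitted. Compare it across arms together with the number of exacerbations, in all children as allocated, by Kruskal-Wallis or an exact test. On the form, define the study period as those 12 weeks and record each stay or the total. Report length of stay among admitted children descriptively, without a test.

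The cost is one line in the variable list and one clarified field on the form; the underlying hospital data are already collected in routine follow-up. The drawback is that many zeros and ties are likely, so the result will be mainly descriptive. The gain is that the comparison keeps the randomised arms and cannot change direction merely through who happened to be admitted.
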